**Figure 2 F2:**
[figure not shown]
Distribution of outcomes across different domains of the ICF. GMFCS, Gross Motor Function Classification System; ICF, International Classification of Functioning, Disability and Health; SDR, selective dorsal rhizotomy; MOSAiC, Medium to longer term Outcomes following Selective dorsal rhizotomy in Ambulatory children with Cerebral palsy.

A study-specific questionnaire (online supplemental SI-3) has been developed in collaboration with the study advisory group of CYP and parents. The questionnaire is designed to capture a comprehensive range of post-SDR outcomes across all ICF domains. The survey content was shaped by the PPI and stakeholder activities, literature review and clinical experience. It includes items related to orthopaedic and pharmacological interventions required after SDR, bladder and bowel function, and sensory issues. The questionnaire also captures current orthotics and mobility aids, physiotherapy input and participation in physical leisure activities. Based on the recommendations of the advisory group members, questions were added to explore the psychological impact of SDR on CYP and their parents, as well as the impact on activities of daily living and engagement in education settings.

Parents and CYPwCP can complete the survey at any point, before, during or after their hospital visit. To accommodate family preferences and reduce any language or accessibility barriers, the questionnaire may be completed on paper, via phone, or in a virtual session with the PI (DC) and a translator. The survey will take approximately 30–50 min to complete. A thank-you voucher will be given to families as a token of appreciation for their time.

#### Primary outcome measures

GMFM-66: The GMFM-66 is a standardised clinical and research tool used to evaluate changes in gross motor function in CYPwCP.^25^ It consists of 66 items assessing a range of gross motor abilities, from lying, rolling, sitting and crawling to walking and jumping. Each item is scored using a 4-point criterion-referenced scoring system on a 0–3 ordinal scale. Final scores will be calculated using the GMFM Scoring App, which converts individual item scores into a total score ranging from 0 to 100, representing low to high gross motor ability, with interval-level measurement properties.^29^ The GMFM-66 is shown to be highly reliable, with intraclass correlation coefficients (ICCs) of 0.99 for test–retest reliability.^29^ The minimum clinically important difference (MCID) for GMFM-66 is estimated to be 1.5 and 1.2 units, corresponding to large effect sizes, for GMFCS level II and III, respectively.^30^

GMFM centiles: The GMFM centile curves represent the relationship between age and gross motor function, as measured by GMFM-66 scores, across different GMFCS levels. These curves depict the average trajectory of motor development, including both the rate of improvement and the maximum expected functional capacity, for CYPwCP between the ages of 2 and 12 years. For those classified as GMFCS level II, GMFM-66 scores typically plateau by around 9 years of age, whereas children in GMFCS level III typically reach peak scores by 8 years of age, followed by a potential decline of approximately 4.7 units during adolescence and into adulthood.^31^ Given the absence of reference data beyond age 12, centiles for 12-year-olds are often applied to older children in research.^32 33^

6-MWT: The 6-MWT is a self-paced, submaximal exercise test used to measure functional walking capacity and endurance in CYPwCP.^24 34^ The test will be conducted on a 25 m track at GOSH, using standardised instructions. Typical walking aids and orthoses, if applicable, will be used, and the distance walked in 6 min will be recorded. Reference values for children aged 4–17 years^35^ and longitudinal developmental trajectories and age-specific reference percentiles for CYPwCP across different GMFCS levels I–III have been published.^36^ The 6-MWT has excellent test–retest reliability (ICC=0.98).^24 34^ The MCID for the 6MWT in CYPwCP is not well established; a range of 20–36 m for GMFCS level II and 23–46 m for level III has been reported in the literature.^37^

Cerebral Palsy Quality of Life (CPQOL): The CPQOL is a validated tool designed to assess health-related QoL for CYPwCP across 5–7 domains.^38^ These include social well-being and acceptance, feelings about functioning, participation and physical health, emotional well-being and self-esteem, access to services, and pain and impact of disability. Items are rated on a nine-point rating scale, with domain scores calculated by averaging responses and converting them to a 0–100 scale, where higher scores indicate better QoL. There are two self-report versions, CPQOL-Child (for children aged 9–12 years) and CPQOL-Teen (for adolescents aged 13–18 years), and two proxy-report versions, completed by primary caregivers for children aged 4–12 and adolescents aged 13–18. The CPQOL has good internal consistency, ICC ranging from 0.74 to 0.92 for children and 0.81 to 0.96 for teens, and adequate test–retest reliability ranging from 0.76 to 0.89 for children and 0.59 to 0.83 for teens.^38 39^ Currently, there are no published MCID values for the CPQOL.

#### Secondary Outcome Measures

MAS: The MAS is a widely used clinical tool for assessing muscle tone by measuring resistance to passive movement during a high-velocity stretch.^27^ The limb is moved through its available range of motion, and resistance is graded on a 6-point ordinal scale, from 0 (no increase in tone) to 4 (rigid limb). The scale includes an intermediate score of 1+to capture subtle increases in tone. The inter-rater agreement has been reported with a mean ICC of 0.686 (95% CI 0.563 to 0.780) and a kappa coefficient (κ) of 0.360 (95% CI 0.241 to 0.468). The intrarater agreement shows an ICC of 0.644 (95% CI 0.543 to 0.726) and a κ of 0.488 (95% CI 0.370 to 0.591).^40^ The MCID for MAS in CYPwCP has not been established.

TUG: The TUG is a functional mobility test used to evaluate dynamic balance and anticipatory postural adjustments in CYPwCP.^26^ Participants are instructed to rise from a chair, walk 3 m to touch the wall and return to sit down as quickly as possible, without running. Usual walking aids and orthoses are used as needed. The TUG has excellent inter-rater reliability (ICC: 0.83–0.99).^41^ Minimal detectable change values range from 1.40 to 8.74 s, and MCID estimates range from 0.22 to 5.31 s in children aged 3 to 10 years.^41^

Edinburgh Visual Gait Analysis (EVGS): The EVGS is a video-based observational tool used to assess gait deviations in CYPwCP.^42^ It consists of 17 gait parameters measured at six anatomic levels (foot, ankle, knee, hip, pelvis and trunk) representing key features of pathological gait in CYPwCP. Each parameter is scored on a 3-point ordinal scale (0=normal, 1=moderate deviation, 2=marked deviation), resulting in a total score ranging from 0 (normal gait) to 34 (maximal deviation). The EVGS has excellent inter-rater (ICC2,1=0.90–0.97) and intrarater (ICC2,1=0.91) reliability.^43^ There is a large variation in the MCID values reported in the literature, ranging from 2.4 to 15 points. The MDC^90^ of 6.0^43^ and the MCID of 2.4 points^44^ have been proposed.

Gait Outcome Assessment List (GOAL) (child version): The GOAL is a validated questionnaire designed to determine gait-related priorities and functional mobility for ambulant CYPwCP.^45^ It comprises 48 items across seven domains, with scores standardised on a 0–100 scale, where higher scores indicate better function. Item scores are summed and averaged to generate domain-specific and total scores. Moderate to strong test–retest reliability has been reported for the parent version (ICC, total score: 0.98 and domain scores: 0.69–0.93).^45 46^

Functional Mobility Scale (FMS): The FMS is a validated tool used to assess functional mobility in CYPwCP, aged 4–18 years, across three distances: 5 m, 50 m and 500 m, representing typical home, school and community distances. For each distance, the use of assistive devices is rated on a 6-point ordinal scale, where 1 indicates wheelchair use and 6 indicates independent ambulation.^47^ The FMS demonstrates strong inter-rater reliability with quadratic weighted kappa coefficients ranging from 0.86 to 0.92 for the three distances.^48^ A change of one level is considered a clinically meaningful change.^49^

Functional Assessment Questionnaire (FAQ): The FAQ is a 10-point ordinal scale used to rate a child’s typical walking ability in community environment.^50^ It is a performance-based measure, with scores ranging from 1 (cannot take any steps at all) to 10 (walks, runs and climbs on level and uneven terrain without difficulty or assistance). It exhibits good inter-rater reliability (ICC=0.81) and intrarater reliability (ICC=0.92).^50^

#### Phase 2: qualitative data collection

Semistructured interviews will be conducted with a subset of parents and CYP using a topic guide (online supplemental SI-4), developed in collaboration with the study advisory group. Participants may be recruited from the same or different families. Parent interviews will explore their prior expectations of SDR and reflections, experiences and perceptions of the SDR surgery, post-SDR rehabilitation and any subsequent interventions. The interviews will also delve into perceived facilitators, barriers and challenges encountered during the SDR rehabilitation journey. Parents’ preoperative goals and expectations, satisfaction with outcomes and perspectives on their QoL will be explored.

Interviews with CYP will be adapted for their age, cognitive levels and communication abilities. Semistructured interviews will be used to discuss their participation in daily life, feelings about their abilities and challenges, social interaction and future goals. CYP will be offered the choice of having their main carer present in a supporting capacity. While older CYP are likely to engage in conversations, younger children will be offered the use of creative adjuncts such as drawing, ‘Play-Doh’, Lego, personal photographs and videos taken by the family as a memory aid. These interviews will prioritise the voice of CYP.

The interviews will be conducted either in person or virtually, according to the preferences of parents and CYP. Interviews will last approximately 30–60 min for CYP and 45–90 min for parents. All interviews will be audio-recorded and transcribed verbatim by an external transcription service approved by the Trust’s Research and Development department. Transcripts will be checked for accuracy against the recordings by the PI (DC). The researcher will also take notes during the interview and write a postinterview reflection to support the qualitative analysis.

### Data analysis

The data from the quantitative and qualitative phases will be analysed separately before being integrated during the interpretation phase, in line with the convergent parallel mixed-methods research design.

#### Phase 1: quantitative data analysis

Descriptive analysis will be used to provide participants’ demographic and baseline characteristics. Continuous variables will be summarised using mean and SD when normally distributed, or median and IQR when skewed. Categorical variables will be presented as frequencies and percentages. Association between categorical variables will be examined using cross-tabulation and χ² tests. The primary and secondary outcome measures (GMFM-66, GMFM-66 centile scores, 6-MWT, CP QOL, TUG, FMS and FAQ) will be compared between baseline and subsequent follow-up time points. Generalised linear equation models will be used to analyse longitudinal data across multiple time points. Univariate analysis will be conducted to explore associations between individual predictors and outcome variables. Non-parametric tests will be applied to ordinal outcome measures (FMS, FAQ and SMC). A multiple regression model will be created to identify predictors of favourable outcomes, incorporating relevant covariates.

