**Methods and analysis:**

This is a convergent parallel mixed-methods study using the International Classification of Functioning, Disability and Health as a theoretical framework. The study aims to recruit 90 CYPwCP participants, who had SDR at a tertiary hospital in the UK when aged between 3 and 14 years. Participants (parents and CYPwCP) will be invited to complete an online survey and attend the hospital for one follow-up visit 3 or more years after SDR. Comparisons will be made with existing data on objective measures and parent-reported outcomes collected in clinical practice at baseline, 6, 12 and 24 months to understand the trajectory of changes. Semistructured interviews will be conducted with 18–20 parents/carers and 25–30 CYPwCP to understand their perspectives on the outcomes of SDR compared with their prior expectations. The Framework Method will be used to analyse qualitative data both inductively and deductively. Qualitative and quantitative study data will be integrated using joint displays.

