Short-term outcomes of SDR, up to 2–3 years after surgery, are well-established, particularly in reducing spasticity and improving gross motor function.^11 12^ However, evidence for longer-term benefits in gross motor function and participation remains inconclusive, as highlighted in a recent systematic review.^13^ Despite the lack of clear evidence for longer-term benefits of SDR over other interventions, SDR continues to be offered at various centres worldwide, supported by findings from long-term observational studies using a variety of outcome measures.^14 15^ In shared decision-making, clinical decisions regarding the suitability of the SDR procedure occur alongside families’ expectations. Parental decision-making is frequently influenced by hopes of long-term benefits such as reduced orthopaedic interventions and improved quality of life (QoL).^16^ This has also been a strong focus from our patient and public involvement (PPI) activities. Families regularly express the need for clearer information on longer-term outcomes to guide their decision-making.^16^

Long-term outcomes following SDR have been identified among the top 10 research priorities in both the Childhood Disability and Paediatric Lower Limb Surgery James Lind Alliance Priority Setting Partnerships.^17 18^ There is a knowledge gap in the evidence on the effects and impact of SDR on CYP’s physical functioning and QoL within the UK healthcare context in the medium to longer term. Under the current NHSE SDR pathway, CYPwCP are seen for up to 2 years at a specialist centre, after which care is managed by local community services.^9^ Currently, there is no national CP register in the UK to capture the longer-term outcomes of CYPwCP who have undergone SDR. Furthermore, CYPs and parents’ experiences, prior expectations and perceptions of outcomes of SDR and rehabilitation remain underexplored. Capturing the voices of CYPs and parents is central to strengthening the evidence base and better supporting their needs, and informing their decision-making and expectations.

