### Study sample and recruitment

This single-centre study will be conducted at Great Ormond Street Hospital for Children (GOSH), a paediatric tertiary hospital in London, UK. Inclusion criteria are CYPwCP who had SDR surgery at GOSH at least 3 years prior and were classified as GMFCS level II or III at the time of surgery. The GMFCS is a five-level ordinal classification system that categorises CYPwCP based on gross motor abilities, mobility limitations, need for assistive devices or wheeled mobility.^7^ Children in levels I and II are able to walk independently with some difficulty, while those at level III walk using a walking aid (online supplemental SI-1). The NHS England selection criteria for SDR eligibility are outlined in online supplemental SI-2. Participants will be eligible for this study if they completed a baseline assessment prior to SDR and have at least one follow-up assessment at 6, 12 or 24 months postsurgery. Parents of eligible CYPwCP will also be invited to participate. For those who have recently undergone orthopaedic surgery or received botulinum toxin injections in the lower limbs, data will be collected 3–9 months after that procedure, allowing time for recovery. This decision will be based on the type of procedure and in consultation with CYPwCP and their families, consistent with routine practice.

Based on the eligibility criteria, a minimum of 182 participants has been identified from the GOSH SDR database for inclusion in the observational cohort study (phase 1). All CYPwCP and parents participating in phase 1 will be eligible for the qualitative study (phase 2). Purposeful sampling will be used to identify CYPwCP and parents, ensuring a diverse representation of participants based on the GMFCS level, age at surgery, length of follow-up and outcomes at 2 years after SDR. The concept of ‘information power’, where the more relevant and high quality information the sample holds, the lower the number of participants needed, is used to determine the sample size.^23^ Based on this premise and previous qualitative research experience, a sample of approximately 18–20 parents and 25–30 CYPwCP is anticipated to provide maximum variation and depth to explore a range of experiences and perspectives.

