### Procedures

#### Phase 1: quantitative study

Participants (parents and CYPwCP) will complete an online survey via REDcap, followed by a single study visit for a clinical assessment. The clinical assessment will start with more physically demanding assessments, such as the 6-Minute Walk Test (6-MWT),^24^ Gross Motor Function Measure (GMFM),^25^ Timed Up and Go (TUG),^26^ followed by evaluation of muscle tone using the Modified Ashworth Scale (MAS)^27^ and lower limb passive joint range of movement. The assessment protocol mirrors standard clinical practice, and all participating CYPwCP will be familiar with this process. All assessments will be conducted by the PI (DC), supported by a clinical physiotherapist or physiotherapy assistant.

The outcomes and outcome measures were selected based on the findings from a scoping review on the outcomes used in the SDR literature,^28^ NHSE commissioning guidelines and acceptability and meaningfulness to parents and CYPwCP (as informed by the PPI and study advisory group). The selected outcomes and measures are presented in table 1 and the mapping of outcomes across the domains of the ICF is illustrated in figure 2.

**Table 1 T1:** Outcomes measures included in this study

	Measure	Administration
Classification	Gross Motor Function Classification System–Family report Questionnaire	Questionnaire
Primary outcome measures	Gross Motor Function Measure-66 and centiles	Clinician-assessed
	6-Minute Walk Test	Clinician-assessed
	Cerebral Palsy Quality of Life	Questionnaire–Parent-proxy and CYP-reported
	MOSAiC Study Questionnaire	Questionnaire–Parent-reported
Secondary outcome measures	Modified Ashworth Score	Physical examination
	Timed Up and Go	Clinician-assessed
	Edinburgh Visual Gait Analysis	Clinician-assessed
	Gait Outcome Assessment List–Child Version	Questionnaire–CYP-reported, with assistance from parent carer, if needed
	Functional Mobility Scale	Questionnaire–Parent and CYP-reported
	Functional Assessment Questionnaire	Questionnaire–Parent-reported

CYP, children and young people; MOSAiC, Medium to longer term Outcomes following Selective dorsal rhizotomy in Ambulatory children with Cerebral palsy.

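### Surgery after SDR accumulates over 3 to 10 or more years, but the only explicit methods for categorical data (percentages, chi-square) take no account of time at risk

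*Protocol article*

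**What the plan says.** The section Phase 1: quantitative data analysis deals with categorical data in two sentences: "Categorical variables will be presented as frequencies and percentages", and "Association between categorical variables will be examined using cross-tabulation and χ² tests". The longitudinal comparison is then given for a named list: "GMFM-66, GMFM-66 centile scores, 6-MWT, CP QOL, TUG, FMS and FAQ) will be compared between baseline and subsequent follow-up time points". The study questionnaire is not on that list.

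Table 1 places the "MOSAiC Study Questionnaire" among the primary outcome measures. Of its content, the text below Figure 2 says: "It includes items related to orthopaedic and pharmacological interventions required after SDR, bladder and bowel function, and sensory issues".

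Time since surgery varies widely. Eligible children "had SDR surgery at GOSH at least 3 years prior", with no upper limit in that section, and the abstract says that they will "attend the hospital for one follow-up visit 3 or more years after SDR". The aims speak of a medium-term band (3–5 years) and a long-term band (6–10 years).

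The Introduction names "hopes of long-term benefits such as reduced orthopaedic interventions" as an example of what influences parents, alongside quality of life. The strengths and limitations box concedes that unequal time since SDR, and later interventions, may confound attribution. The analysis section does not name time since SDR.

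**The concern.** Whether a child has had orthopaedic surgery since SDR is a cumulative event: the proportion can only rise as follow-up lengthens. One child may report on 3 years and another on 10 or more.

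Two things follow if the stated methods are applied to it.

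- The overall percentage has no time horizon. It depends on how many recently and how many long-ago operated children happen to take part, and it cannot tell a family the risk by 5 or by 10 years.
- A chi-square test between groups with different follow-up responds to the difference in exposure as well as to any difference in risk.

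The outcome matters to the study. Musculoskeletal outcome is in research question 1 and orthopaedic outcome in question 3, and the Discussion says that the results will help prepare families for possible further orthopaedic or drug treatment.

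**Working it through.** The article gives no intervention rate, alpha or split between the bands, so there is no figure of the plan's own to reproduce. The check illustrates the mechanism.

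**Inputs from the article.** Planned sample 90; one late visit per child; at least 3 years since SDR; bands of 3–5 and 6–10 years.

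**Assumptions.** The same constant hazard of first surgery for every child, 8% a year (range 4–12%); 45 children per band; follow-up uniform over 3 to <6 and 6 to <11 years; two-sided alpha 0.05; uncorrected chi-square.

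**Step 1: cumulative proportion.** P(t) = 1 − exp(−hazard × t).

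| Hazard per year | 3 years | 5 years | 10 years |
|---|---|---|---|
| 4% | 11% | 18% | 33% |
| 8% | 21% | 33% | 55% |
| 12% | 30% | 45% | 70% |

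At 8%: 1 − exp(−0.24) = 0.213 and 1 − exp(−0.80) = 0.551.

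**Step 2: the pooled percentage depends on the mix.** At the band midpoints (4.5 and 8.5 years) and 8% a year, the proportions are 1 − exp(−0.36) = 0.302 and 1 − exp(−0.68) = 0.493.
- 60 medium-term and 30 long-term children: (60 × 0.302 + 30 × 0.493)/90 = 37%.
- 30 and 60: (30 × 0.302 + 60 × 0.493)/90 = 43%.

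The underlying risk is the same in both cases.

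**Step 3: chi-square between the bands, by hand.** Difference 0.493 − 0.302 = 0.191; mean proportion 0.398.
- Standard error under equality: √(2 × 0.398 × 0.602/45) = 0.103.
- Standard error under the two proportions: √((0.302 × 0.698 + 0.493 × 0.507)/45) = 0.101.
- z = (0.191 − 1.96 × 0.103)/0.101 ≈ −0.11, so the probability of a significant result is about 46%.

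**Step 4: the same by simulation.** With 4,000 runs per setting and individual follow-up times, the test was significant in 30%, 45% and 53% of studies at 4%, 8% and 12% a year. Over a wider range of assumed rates (3–15% a year) the result was 25–59% with 45/45 children and 19–57% with 30/60.

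**Step 5: where the effect weakens or vanishes.** At 3–15% a year:
- partly overlapping follow-up (3–9 v 5–11 years): 8–19%;
- the same follow-up distribution in both groups: 4–6%, the nominal level.

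**Step 6: does using time at risk remove it?** A person-time rate-ratio test on the simulated band data of step 4 (3–15% a year) was significant in 2.6–5.4% of studies.

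**The case against.** The strongest reply is that the article nowhere plans the test illustrated here. The chi-square sentence stands in the descriptive opening of the analysis section and names neither the questionnaire, nor orthopaedic surgery, nor a contrast of the bands. That is right. A reader might infer that a planned test has a 45% type I error; the documents do not support this. No such contrast is stated. Moreover, the cumulative proportions in the two bands do differ in the illustration, so the test detects a real difference in burden. It misleads only if that difference is read as one of risk.

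A reader might also infer that contrasts by GMFCS level or age at surgery would be falsely positive. Nothing in the article shows that either is related to time since SDR, and with balanced follow-up the chi-square test is sound.

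It can also be said that the univariate analyses and the multiple regression for predictors of favourable outcomes could take in time since SDR. They could, but the covariates are not named and interventions are not mentioned there.

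The questionnaire itself is in a supplement that is not shown, so it is unknown whether its items record dates, counts or current use. Drug items in particular may not be first-event data. This limits the point to orthopaedic surgery unless the items say otherwise.

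Finally, an article may leave detail to a fuller document. But here methods for categorical variables are stated, and they do not suit a cumulative outcome seen after unequal follow-up. That is more than missing detail.

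**Conclusion.** The point holds in a limited form. The only explicit methods for categorical variables ignore time at risk, the primary-listed questionnaire is outside the longitudinal list, and the confounding conceded among the limitations is not carried into the analysis.

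- **Pooled percentage:** without a defined time point, whatever the true rate.
- **Comparison of the two bands, if made:** exposure and risk are certainly mixed. The figure of about 45% (30–53%) rests on an assumed equal constant hazard of 8% (4–12%) a year and 45 children per band.
- **Other factors:** affected only if related to time since SDR.

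This should be corrected before analysis. It does not affect the continuous primary measures.

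**What to change.** In Phase 1: quantitative data analysis, add a sentence or two on interventions after SDR:

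- Report first orthopaedic surgery after SDR as cumulative incidence at fixed years since SDR (such as 3, 5 and 10), censored at the survey or visit, with events per person-year.
- Examine factors with Cox regression.
- Where only yes/no is recorded, use complementary log-log regression with log(years since SDR) as an offset. Enter it as a covariate instead to relax the constant-hazard assumption.
- Treat drug interventions in this way only where the items record events since SDR rather than current use.
- Keep chi-square for variables that do not accumulate with follow-up.

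The cost is mainly wording. The time-to-event analysis needs the date or year of first surgery, from the questionnaire or the notes; the yes/no model needs only the dates of SDR and survey. The downsides are recall error in procedure dates and, with the offset, a constant-hazard assumption that may not hold in growing children.
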